### Power calculations

For power analyses, we used Monte Carlo methods. Starting at randomization with both conditions at 20%, we have 80% power to detect a change where 54% of the patients in sites in the better facilitation condition are provided MOUD by the last quarter, compared to 45% of the patients in the poorer performing arm. This power calculation allows for moderate variation among the sites’ rates at baseline, in the slopes, and at each measurement time. The approach to the effectiveness measure, 6-month retention rate, will proceed similarly.

We will utilize latent linear growth modeling to understand the impact on the secondary composite continuous measure outcomes (e.g., IMAT; SIC). The impact will be identified as the difference in slopes for the two implementation strategy conditions, fit using maximum marginal likelihood, and tested using a Wald-type test on the difference in slopes divided by the corresponding standard error. Monte Carlo simulation was used to examine how the model’s parameters affect statistical power. With type I error of 5%, and conservative measurement error of 20% at each time point, we have 80% power to detect an effect size of 0.77 (54 randomized sites) and conservatively 0.81 (49 randomized sites). We note that in a previous head-to-head randomized implementation trial of 51 sites, we were able to find significant differences in implementation outcomes.

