All programs that do not achieve or sustain target outcome criteria by the end of Phase 3 (12 months from baseline) will be randomized to either of the remaining two implementation strategies—NIATx Internal Facilitation (NIATx-IF) and NIATx External Facilitation (NIATx-EF). The NIATx-IF strategy features an internal change leader (employee) who will help other staff gain skills and efficacy to implement changes and address barriers in attitude and beliefs. Thus, determinants at the individual and organizational levels are the focus of the NIATx-IF implementation strategy (Fig. 2). NIATx-EF is an evidence-based implementation strategy that is widely used and studied [45]. NIATx-EF features an external expert or coach. The coach leverages their expertise and knowledge to guide staff in implementing changes, help employees gain confidence and skills, and address potential obstacles including stigma and attitudes [22, 48]. For the same reasons as NIATx-IF, NIATx-EF is tailored to issues at the organization and individual levels. IF and EF models have been systematically studied and compared [46, 49, 50]. Although there is evidence for both IF and EF, with better outcomes for EF, the cost for EF is likely greater than for IF [49]. Using the procedures employed in a previous implementation trial, we will balance the two groups before randomization [51]. We will then use a randomized cluster group trial design to compare NIATx-IF to NIATx-EF.

In our study design, programs that “graduate” to the sustainment/follow-up arm but then fail to maintain the criteria of success for two consecutive quarters will have two opportunities to rejoin the active implementation strategy phases (Fig. 3). The first opportunity where a program on Path 1 could re-enter is at the end of Phase 3 if they do not sustain improvements after receiving the EMF strategy. The second opportunity for a program on Path 2 to re-enter would be at the end of Phase 4 if they do not sustain improvements after receipt of the EMF and NIATx/MAT Academy implementation strategies. There are thus five possible paths a program might take in this study. Months in the active implementation stage range from 6 (Path 1) to 30 (Path 5). The sustainment period ranges from 12 months (Path 5) to 36 months (Path 1). The path followed by a program depends on when it meets (and sustains) implementation targets.

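### The likelihood fit and Wald-type test named for the continuous outcomes (IMAT, SIC) run slightly above the stated 5% type I error with 49 to 54 sites: about 5.4% to 6.1% before allowing for balancing

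*Protocol article*

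**What the plan says.** The second paragraph of Power calculations in the protocol article sets the method and the scope: "We will utilize latent linear growth modeling to understand the impact on the secondary composite continuous measure outcomes (e.g., IMAT; SIC"). The arm effect is the difference in slopes, "fit using maximum marginal likelihood, and tested using a Wald-type test on the difference in slopes divided by the corresponding standard error".

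The same paragraph reports the power: "we have 80% power to detect an effect size of 0.77 (54 randomized sites) and conservatively 0.81 (49 randomized sites"). The conditions set for that result are stated just before it: "With type I error of 5%, and conservative measurement error of 20% at each time point". No reference distribution for the ratio, restricted likelihood or other small-sample correction is mentioned.

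The unit of randomization is the program. The section on implementation strategies says "We will then use a randomized cluster group trial design to compare NIATx-IF to NIATx-EF" and, in the sentence before, that the two groups will be balanced ahead of randomization by procedures from an earlier trial. The balancing factors are not listed.

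**The concern.** Facilitation arm varies only between sites, so the slope difference is in effect a two-sample comparison of about 54 (or 49) site slopes, however many quarters or patients lie beneath them. At that sample size two common shortcuts matter slightly. Maximum likelihood divides the between-site sum of squares by n rather than n−2, which makes the standard error a little too small. A Wald ratio is usually compared with the normal distribution rather than a t, which makes the critical value a little too small. The article names the first and, by its wording, suggests the second.

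At stake is whether the stated 5% is the error rate that the named test has, and whether the detectable effects were calculated for a test that holds 5%. This is more than an omitted detail, because the article itself puts an estimator, a type of test and an error rate side by side.

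**Working it through.** **Inputs.** From Power calculations: n = 54 or 49 sites, type I error 5%, power 80%, effect sizes 0.77 and 0.81. Assumed because not stated: two-sided testing, 1:1 allocation (27/27 and 24/25), complete balanced data, and effect size in SD units of the site slopes.

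**1. Reproduce the stated power.** The standard error in SD units is √(1/27 + 1/27) = 0.272 for 54 sites and √(1/24 + 1/25) = 0.286 for 49.
- Normal approximation: 0.77/0.272 − 1.96 ≈ 0.87, so power is 80.8% with 54 sites. For 49 sites at 0.81 it is 80.9%.
- Noncentral t on n−2 df: 79.3% in both cases.
- Likelihood standard error with a normal reference: 81.6% and 81.8%.

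All lie within 2 points of 80%. The stated figures are reproduced, but they do not show which test was used.

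**2. True size of the named test.** With balanced data and arm-specific intercepts, the likelihood variance is SS/n instead of SS/(n−2). The ratio exceeds a critical value c exactly when |t| > c·√((n−2)/n), where t has n−2 df. So size = 2·P(t with n−2 df > c·√((n−2)/n)).

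| Standard error | Reference | 54 sites | 49 sites |
|---|---|---|---|
| ML | normal | 5.99% | 6.10% |
| ML | t, n−2 df | 5.43% | 5.47% |
| unbiased | normal | 5.54% | 5.59% |
| REML | t, n−2 df | 5.00% | 5.00% |

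For the first row the thresholds are 1.96·√(52/54) = 1.923 and 1.96·√(47/49) = 1.920.

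**3. Check by simulation.** One million replicates of the reduced test (ML, normal reference) gave 5.98% and 6.09%. Full ML fits of a random-intercept, random-slope model gave 5.4% to 6.9% with a normal reference. These covered seven settings (4 or 10 time points, with or without an arm difference at baseline) with 4,000 replicates each, a simulation standard error of about 0.4 points, and assumed variance components.

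**4. Allow for balancing.** Suppose a balanced factor explains a share R² of the slope variance and the analysis ignores it. The arm difference then varies less than the test assumes, and the size is approximately 2·P(t with 52 df > 1.923/√(1−R²)). With 54 sites, ML and a normal reference:
- R² = 5%: threshold 1.973, size about 5.4% (simulation 5.3% to 5.4%).
- R² = 8%: threshold 2.005, size about 5.0%.
- R² = 10%: threshold 2.027, size about 4.8% (simulation 4.7% to 4.8%).

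If one such factor is included in the model, the residual df fall to 51. The threshold becomes 1.96·√(51/54) = 1.905 and the size is about 6.2%.

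**5. Detectable effects at 80% power, no measurement-error allowance.** A t-test on n−2 df gives 0.777 (54 sites) and 0.817 (49 sites). ML with a normal reference gives 0.754 and 0.791. The article states 0.77 and 0.81.

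**The case against.** The strongest reply has four parts.

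- **The reference distribution is not stated.** The article says Wald-type and does not name the normal. This stands: a reader might infer that the test runs at 6% without qualification, and the text does not support that. With a t reference the excess falls to about half a point. It does not vanish, because the likelihood standard error is still too small.
- **This is detail for the analysis plan, and 5% is only the nominal level in a power simulation.** This stands in part. The degrees-of-freedom method would normally be left to the analysis plan. The estimator, however, is stated here, and it misses the stated 5% on either reference in the balanced case before balancing is considered.
- **Balancing makes an unadjusted test conservative.** This is correct and could offset the excess completely, as step 4 shows. But the offset depends on an unknown R² and works only if the balancing factors are left out of the model. Including them brings the size back to about 6% with a normal reference.
- **The effect is small.** Also correct. The excess is at most about one point in the closed form, and power is still 79.3%. The section calls these outcomes secondary, although Table 3 lists change in IMAT among the Aim 1 primary outcomes.

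Two further inferences should not be drawn. First, a reader might extend the point to the primary binomial growth model. The Data analysis section says only that the effect is tested through a coefficient and names no Wald test, so the document does not support that. Second, a reader might inflate the detectable effects further for the 20% measurement error. The article does not say what the 20% refers to, and error at each occasion acts on slope variance through the number and spacing of occasions, so no specific larger figure can be justified.

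**Conclusion.** The point holds in limited form and is a refinement, not a threat to the trial. For the continuous growth models, maximum likelihood with a Wald-type ratio on 49 to 54 sites has a true size of about 6.0% to 6.1% with a normal reference and 5.4% to 5.5% with a t on n−2 df, against the stated 5%. These figures assume two-sided testing, 1:1 allocation and complete balanced data, and they precede any allowance for balancing. After balancing, the size may be at or below 5% if the factors are ignored, and is about 6% with a normal reference if they are adjusted for. The detectable effects are hardly affected: about 0.78 and 0.82 under a test that holds 5%, against 0.77 and 0.81.

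**What to change.** Fit the growth models for the continuous outcomes by REML, include the factors used to balance the arms, and test the slope difference against a t distribution with Kenward-Roger or Satterthwaite degrees of freedom (about 50 with 54 sites). Including the factors matters in its own right: it removes the dependence on an unknown R² that an unadjusted test after balancing would have.

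Restate the 80%-power detectable effects under that test, starting from about 0.78 (54 sites) and 0.82 (49 sites), and say how the 20% measurement error enters.

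The cost is a software option, a sentence or two of text, and a detectable effect larger by about 0.01 than the one stated (0.777 − 0.77 and 0.817 − 0.81, each 0.007).

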## Discussion

We considered but rejected two alternative designs for this multi-level stagewise implementation strategy trial. First, we discussed a design that contrasted two packaged multi-component implementation strategies tested head-to-head throughout this study for all sites, much like we conducted in an implementation trial of 51 counties in two states [51]. Unlike this two-state study, it would be inefficient in the current trial to force organizations that did not need a full-blown strategy to receive one. Second, we discussed a SMART design that used multiple randomizations for sites not meeting criteria rather than the single one used in this trial. While such a design would in theory allow more insights, multiple randomizations would sacrifice the expected large sample size of 58 sites that powerfully compare NIATx-IF versus NIATx-EF in this trial. We concluded that a study of a stepped and stagewise approach to implementation, within an innovative adaptive implementation design, although unprecedented, has the risk-reward potential for higher relevance and impact.

We also wrestled with a variety of imperfect approaches to evaluating outcomes, both as “measurement-based implementation targets” and as primary outcomes. We selected *reach* because it is standard in MOUD research and practice. The proportion of 50% on MOUD is based on the current state (~ 15%), expert recommendations, options for patient preference, and benchmarks for system-level management of chronic conditions [85]. Since 50% may prove to be a minimum threshold, we may, as a contingency, adjust this proportion or instead examine reach as a continuous variable. The criterion for *adoption* values the integrated prescriber over linked or coordinated access. This increases the likelihood that patients will not fall through the cracks between provider locations. Third, for *implementation* quality, we decided on an IMAT Total Score of 3 or more based on previous systems-level research with other organizational measures, and our recent work with the IMAT. A score of 3 represents an adequate capability. Higher scores, up to 5, reflect enhanced practice, and as a continuous measure, we expect to see IMAT scores rise through the *maintenance* phase. As a proxy for *effectiveness*, the Addiction Care Cascade provides metrics for reach, *timely access* (< 72 h to start medication), and *retention* (continuous care for 6 months). New data on 6-month retention outcomes reveal this as a bare minimum for MOUD quality care [86]. For this study, the 6-month retention rate is feasible and remains a quality standard for MOUD services research.

Efforts to combat the US opioid epidemic have focused on expanding access to MOUD. While there are indications of improved reach and adoption, an ironic gap persists—only about one third of specialty addiction treatment organizations offer MOUD. The SITT-MAT study not only advances the science of implementation but will advance our empirical understanding of how to best respond to a substance-related epidemic by checking all the boxes of expert recommendations to specify, tailor, and track implementation strategies and provides generalizable knowledge useful for systems and organizations. Our protocol leverages the enhanced rigor of advanced implementation scientific approaches to the challenge of installing and sustaining MOUD in a real-world setting, specialty addiction programs. To advance implementation research, we not only open the “black box” of implementation strategies, but we also thoroughly study the contents using a highly unique approach. This study will deploy an adaptive implementation strategy design that has never been done before. The design embeds an evaluation of non-randomized steps as well as a randomized step of implementation strategies into the overall analysis. The approach has elements of both a sequential multiple assignment randomized trial (SMART) design [49, 50, 87–89] and a criterion-based design that employs a measurement-based stepped implementation-to-target approach within an adaptive trial design to improve access to MOUD. The findings have the potential to advance drug abuse treatment research by identifying an optimization of strategies to implement MOUD.

## Data Availability

Not applicable.

## Abbreviations

CFIR: Consolidated Framework for Implementation Research
COINS: Costs of Implementing New Strategies
DDCAT: Dual Diagnosis Capability in Addiction Treatment
EF: External facilitation
EMF: Enhanced monitoring and feedback
EPIS: Exploration, Preparation, Implementation and Sustainment
HCA: Health Care Authority
HEAL: Helping to end addiction long term
ICS: Implementation Climate Scale
IF: Internal facilitation
ILS: Implementation Leadership Scale
IMAT: Integrating Medications for Addiction Treatment
IMAT-SC: Integrating Medications for Addiction Treatment in Specialty Care
MAT: Medications for Addiction Treatment
MOUD: Medications for opioid use disorder
NIATx: Network for the Improvement of Addiction Treatment
NIDA: National Institute on Drug Abuse
OUD: Opioid use disorder
RE-AIM: Reach, Effectiveness, Adoption, Implementation and Maintenance
SIC: Stages of Implementation Completion
SITT-MAT: Stagewise Implementation-To-Target–Medications for Addiction Treatment
SMSS: Sustainment Measurement System Scales
